**Methods:**

The primary aim of this online study is to test the effect on remission rates in cancer patients (primary outcome) with distinct self-selected dietary patterns (omnivore, lacto-ovo-vegetarian, vegan), and allow for an estimation of the effect size. Secondary outcomes are tumor behavior, relapse-free interval, therapies, therapy tolerability and side-effects, comorbidities, medication, quality of life, acceptance, and feasibility of the selected diet. Safety concerns exist for vegan diets (especially in cancer patients) and the study will carefully monitor for deterioration of health, tumor progression, or malnutrition. Furthermore, the study will evaluate the online portal as a study platform (technical and safety aspects, and sequence of displayed questionnaires) as well as the validity of self-reported and online-generated data.

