### Measures and Evaluation Procedures

The primary outcome of this study is defined as complete tumor remission, and calculated as the rate of complete remissions at 6 months by intention-to-treat (ITT) analysis.

Secondary outcomes include tumor history, further classifications of tumor behavior (complete remission, partial remission, no change, or progression), relapse-free time (in months), survival rates for end stages, previous and current tumor therapies (including tolerance and side effects), comorbidities (eg, high blood pressure, stroke), as well as medications unrelated to the tumor (including dosage and intake plan). The determination of tumor behavior during the study period will be evaluated by two investigators, each using independent radiological and laboratory reports.

Data regarding previous nutritional history, the chosen diet during study participation, acceptance and feasibility of the chosen diet, frequency of dietary pattern change, extent and duration of nutritional changes, and the type and strength of support for nutritional changes will also be assessed. In addition, during baseline and follow-up surveys, adherence to dietary patterns will be cross-referenced by food frequency questionnaires (FFQs), which were specifically adopted for discrimination of plant- and animal-derived foods. Participants were also asked to self-report any unplanned change in diet during study participation. Nutritional status of participants will be evaluated using body weight (kg), BMI (kg/m^2^), laboratory test results (eg, albumin), and questions referring to eating problems. Results referring to nutrition and dietary patterns will be evaluated in terms of change and duration of change in dietary patterns (in months).

Study questionnaires also contain questions referring to quality of life covering the Karnofsky Index, as well as additional dimensions (ie, psychosocial wellbeing, psychosocial support). Online questionnaires were designed to be self-instructive and self-evident (Multimedia Appendix 3). In order to evaluate these parameters, questions pertaining to the study platform and interaction with the study team were also included in the questionnaires. The list of parameters included in the study questionnaire was designed to examine all study objectives, and is detailed in Multimedia Appendix 4.

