### Nutrition Safety

To ensure timely detection of the deterioration of nutritional and/or health status of the patients in this study, an intermediate data evaluation is planned, and will include all participants registered before January, 2016. This evaluation will examine tumor staging and the nutritional status of all participants. If this evaluation demonstrates a significantly increased risk of health deterioration in one diet group compared to the omnivorous group, the study will be stopped preterm.

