### Statistical Analyses

Statistics regarding safety issues will be performed in July, 2016 and a complete evaluation will be performed in January, 2017. Comparison of dietary groups in regard to primary and secondary end points will be performed as ITT. Data will be analyzed and adjusted for possible confounders (eg, gender, age, tumor type, tumor stage, weight status, accompanying treatment) and stratified by sex, age, type of tumor, tumor staging, and oncological therapy. Changes over time (eg, weight changes) will be analyzed by paired sample tests. Unpaired tests will be used when making comparisons between cohorts. Descriptive statistics will be used to summarize parameters such as comorbidities, oncological therapies, and additional therapies. *P*-values of <0.05 will be considered significant.

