### Recruitment and Dropout Rates – Preliminary Experiences

As of May, 2016, 530 participants filled out the checklist and 242 (45.7%) have registered for the study. Most respondents were female (174/242, 71.9%), while 68 were male (28.1%). Mean age was 54.7 years (standard deviation 11.7). Most participants were recruited in German speaking countries (Germany, Austria, and Switzerland). As shown in Figure 1, most participants found the website via the Internet or social media (eg, Facebook and Twitter).

Dropouts occurred at each stage of the study, from the checklist for eligibility to the third data survey, as shown in Figure 2. After filling out the registration forms, 242 participants received the invitation for their first data survey, which was completed by 138 respondents (57.0%). Some respondents (33/242, 13.6%) sent an incomplete survey, and 68 of the original participants (28.1%) did not send a survey. Dropout rates consider participants who withdrew study participation, died, or did not answer after being reminded by email. Four patients have been reported to have died as of May, 2016.

Three months after completing the first survey, participants received an invitation for the second survey (n=109 as of May, 2016), which was completed by 72 respondents (66.1%). Four participants (4/109, 3.6%) sent an incomplete survey and 33 (30.3%) dropped out of the study at this point. The study is still underway, and participants who did not receive the second and/or third surveys have been excluded from these calculations.

The 6-month data survey was sent to 43 participants who completed the first and second surveys. As of May, 2016, this survey was completed by 33 participants (77%); 2% (1/33) sent an incomplete survey, and 21% (9/33) dropped out of the study at this point. Given the number of participants who enrolled in the study at least 6 months before May, 2016 (n=101), this gives a completers rate of 32.7%.

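### Weight change is assigned to simple paired and unpaired tests that need both a baseline and a follow-up weight, although only about a third of enrolled participants completed the 6-month survey

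*Protocol article*

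**What the plan says.** The Statistical Analyses section of the protocol article fixes the tests. For within-person change: "Changes over time (eg, weight changes) will be analyzed by paired sample tests". For cohorts: "Unpaired tests will be used when making comparisons between cohorts". It also states: "Comparison of dietary groups in regard to primary and secondary end points will be performed as ITT", and it promises adjustment for sex, age, tumor type and stage, weight status and accompanying treatment.

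Weight is a principal nutrition measure. Measures and Evaluation Procedures lists it first: "Nutritional status of participants will be evaluated using body weight (kg), BMI", followed by laboratory results and questions on eating problems. The abstract commits to safety monitoring: "the study will carefully monitor for deterioration of health, tumor progression, or malnutrition". Nutrition Safety plans an interim evaluation of participants registered before January 2016: "This evaluation will examine tumor staging and the nutritional status of all participants". The study stops early if that evaluation shows a "significantly increased risk of health deterioration in one diet group compared to the omnivorous group".

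On retention, Recruitment and Dropout Rates reports 33 completed 6-month surveys among 101 people enrolled at least 6 months earlier: "this gives a completers rate of 32.7" percent. It counts withdrawal, death and non-response as dropout, and four deaths had been reported by May 2016. The Bias section acknowledges attrition bias; the remedies it gives (reminders, newsletters, other contact) aim at retention and not at analysis.

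**The concern.** A paired test uses only people with both values. An unpaired test of weight change between cohorts needs the same two values, so it inherits the same loss. The intention-to-treat statement does not repair this, because the article does not say how a missing follow-up weight is handled. Naming a complete-pairs test in a study that expects heavy attrition is a choice the document makes, not a detail it leaves open.

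Neither simple test takes covariates, so neither can deliver the adjustment promised in the same section. Diets are self-selected and all tumor types and stages are included, so an unadjusted comparison of weight change between cohorts is hard to read.

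At stake is the third study aim, which includes the effect of a vegan diet on deterioration of health and malnutrition. If weight loss makes people less likely to return the later survey, the weight-change result will understate loss.

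**Working it through.** **1. The plan's own figure.** Completers: 33/101 = 32.7%, as printed. The complement is 68/101 = 67.3%.

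**2. The relevant denominator.** Some of the 101 may never have completed a baseline survey (138/242 = 57.0% of registrants did), and no method measures change in a person with no weight. Among baseline completers, chaining the stages gives:

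- 3-month survey completed: 72/109 = 66.1%
- 6-month survey completed among those sent it: 33/43 = 76.7%
- product: 0.661 × 0.767 = 0.507

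So about 51% have a baseline-to-6-month pair and about 49% do not. This is approximate because the stages have different denominators.

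**3. Size of the bias in one cohort's mean.** Suppose weight change and the propensity to stay in are jointly normal with correlation ρ, and a share p stays. Then

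bias = ρ × SD × φ(z)/p, with z = Φ⁻¹(1 − p).

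The documents give no weight data. The SD of 4 kg and the correlations are assumptions.

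| Denominator | p | φ(z)/p | ρ = 0 | ρ = 0.2 | ρ = 0.3 | ρ = 0.5 |
|---|---|---|---|---|---|---|
| Baseline completers, 6 months | 0.507 | 0.787 | 0 | 0.63 kg | 0.94 kg | 1.57 kg |
| Baseline completers, 3 months | 0.661 | 0.554 | 0 | 0.44 kg | 0.67 kg | 1.11 kg |
| All 101 enrolled, 6 months | 0.327 | 1.104 | 0 | 0.88 kg | 1.32 kg | 2.21 kg |

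Example, first row: 0.5 × 4 × 0.787 = 1.57 kg. The first row is the one to use for the 6-month result; the last includes people who may have no baseline weight.

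**4. Cross-check without the normal model.** Bias = (1 − p) × (mean change in completers − mean change in non-completers). With p = 0.507, non-completers losing 1, 2 or 3 kg more than completers give 0.493 × 1 = 0.49, 0.493 × 2 = 0.99 and 0.493 × 3 = 1.48 kg. The order of magnitude is the same, and the bias is zero if the two groups do not differ.

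**5. The contrast with omnivores.** The bias in a difference between two cohorts is the difference of their biases. If selection has the same strength in both, it cancels. The documents give no dropout by cohort, so this part cannot be sized.

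**6. What a longitudinal model can add.** The 6-month survey went to 43 people who had completed the first two. Of these, 33 completed it, 1 sent it incomplete and 9 dropped out (33 + 1 + 9 = 43; the printed 2% and 21% fit 43 and not the printed 33). So 43 − 33 = 10 people have a 3-month survey but no completed 6-month survey. Their 3-month weights would inform the 6-month estimate.

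**The case against.** The strongest reply is that a paired test is a standard choice for within-person change, that the next sentence of the section plans comparisons between cohorts, and that missing-data rules commonly sit in an analysis plan not shown here. The part about cohorts stands: it would be wrong to say that the plan only asks whether each cohort changed. However, the test named for that comparison needs the same pair of weights and cannot be adjusted. An unseen imputation rule could soften the point, but the article names these tests and states no such rule.

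A reader might infer that patients who deteriorate disappear from the safety assessment. The documents do not support that. Online forms for severe deterioration and withdrawal, laboratory results, questions on eating problems, death reports and the interim evaluation all remain. The forms still depend on patients reporting, so they reduce the gap without closing it.

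A reader might also infer that illness is driving dropout. The article lists withdrawal, death and non-response, tabulates no reasons, and attributes attrition to anonymity and lack of contact. Illness-related dropout is plausible but not shown.

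Nor does the plan necessarily discard the 3-month weights. Nothing limits the paired tests to baseline against 6 months, and a baseline-to-3-month test would use them.

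Finally, a mixed model recovers only part of the loss. That is correct and is counted as a downside under the fix.

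**Conclusion.** The point holds for the weight-change result, not for the safety assessment as a whole. The plan fixes complete-pairs tests for a principal nutrition measure although 67.3% of those enrolled at least 6 months had no completed 6-month survey, and although dropout includes deaths. These tests also cannot carry the adjustment that the section promises.

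The bias in a cohort's mean 6-month change is 0 to about 1.6 kg among baseline completers, in the direction of looking safe if those who lose weight leave. This rests on the assumed 4 kg SD, a correlation of 0 to 0.5, and a retention of about 51% chained from different denominators. Bias in the contrast with omnivores arises only if selection differs between cohorts, which the documents neither show nor exclude. The change is worth making because it is cheap and uses weights already collected.

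**What to change.** For weight and BMI, replace the paired and unpaired tests with a linear mixed model for the values at 0, 3 and 6 months. Include cohort, visit, cohort-by-visit and the baseline confounders already listed in Statistical Analyses, and use every participant with at least one weight. Report the cohort-by-visit contrast of each cohort against omnivore as the weight-change estimate, and show deaths and withdrawals per cohort beside it.

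The cost is a change of analysis wording; no new data are needed. The model assumes that dropout is explained by the observed data, which is weaker than what complete pairs require but still cannot be checked. It does not correct for dropout that depends on weights never observed. It gains 6-month information mainly from the roughly 10 people with a 3-month but no completed 6-month survey, adds little for people with a baseline weight only, and nothing for people with no weight. That is why the counts of deaths and withdrawals need to stand next to the estimate.

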## Results

Data collection commenced in April, 2015 and recruitment ended in June, 2016. After completion of the study in December, 2016, data will be analyzed and prepared for publication.

### Recruitment and Dropout Rates – Preliminary Experiences

As of May, 2016, 530 participants filled out the checklist and 242 (45.7%) have registered for the study. Most respondents were female (174/242, 71.9%), while 68 were male (28.1%). Mean age was 54.7 years (standard deviation 11.7). Most participants were recruited in German speaking countries (Germany, Austria, and Switzerland). As shown in Figure 1, most participants found the website via the Internet or social media (eg, Facebook and Twitter).

Dropouts occurred at each stage of the study, from the checklist for eligibility to the third data survey, as shown in Figure 2. After filling out the registration forms, 242 participants received the invitation for their first data survey, which was completed by 138 respondents (57.0%). Some respondents (33/242, 13.6%) sent an incomplete survey, and 68 of the original participants (28.1%) did not send a survey. Dropout rates consider participants who withdrew study participation, died, or did not answer after being reminded by email. Four patients have been reported to have died as of May, 2016.

Three months after completing the first survey, participants received an invitation for the second survey (n=109 as of May, 2016), which was completed by 72 respondents (66.1%). Four participants (4/109, 3.6%) sent an incomplete survey and 33 (30.3%) dropped out of the study at this point. The study is still underway, and participants who did not receive the second and/or third surveys have been excluded from these calculations.

The 6-month data survey was sent to 43 participants who completed the first and second surveys. As of May, 2016, this survey was completed by 33 participants (77%); 2% (1/33) sent an incomplete survey, and 21% (9/33) dropped out of the study at this point. Given the number of participants who enrolled in the study at least 6 months before May, 2016 (n=101), this gives a completers rate of 32.7%.

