### Study Population and Setting

Whenever possible, participants selected one of three defined diets (omnivore, lacto-ovo-vegetarian, or vegan) at baseline. If none of these diets was applicable, participants were classified as having *other diets* (Table 1). Participants were instructed to maintain the chosen diet for 6 months. In addition, respondents were encouraged to continue their prescribed cancer treatment during the study period, and to undergo all recommended follow-up investigations.

Calculation of the required sample size for this study is not possible, as the effect size of the dietary patterns is unknown. Therefore, this study is classified as a pilot study.

The study is being conducted online via a bilingual study website [27]. Registration processes, eligibility assessments, and questionnaires at baseline and follow-ups are all completed online between April, 2015 and December, 2016. Prior to study participation, potential participants performed an online eligibility check (Multimedia Appendix 1), and were asked to provide contact information and a signed patient information and consent form. After registration, participants received an email including their personal login information for the study website, their study identification number, and a link to their baseline questionnaire. Invitations for assessments at 3, 6, 12, and 24 months are delivered by email (Figure 2). If participants do not fill in their questionnaires at the respected time, they are sent reminder emails. In addition to the three main study questionnaires, study participants are asked to report any severe deterioration, unplanned change of their selected diet, or withdrawal from study participation, via online forms (Multimedia Appendix 2).

Ethical approval was obtained from the Ethics Committee of the City of Vienna on February 2nd, 2015 (EK 15-021-VK_NZ).

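### The 6-month survey appears to have been sent conditionally on completing the two earlier surveys, which does not fit a 6-month remission comparison labelled ITT

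*Protocol article*

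**What the plan says.** In the Protocol article, Measures and Evaluation Procedures, the primary outcome is complete remission, "calculated as the rate of complete remissions at 6 months by intention-to-treat (ITT) analysis". Statistical Analyses extends this: "Comparison of dietary groups in regard to primary and secondary end points will be performed as ITT".

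Study Population and Setting gives the contact schedule: "Invitations for assessments at 3, 6, 12, and 24 months are delivered by email (Figure 2". Reminders follow if a questionnaire is late. No invitation is made to depend on having completed an earlier one.

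Recruitment and Dropout Rates – Preliminary Experiences describes what was done by May 2016. The second survey was triggered by the first: "Three months after completing the first survey, participants received an invitation for the second survey (n=109 as of May, 2016". For the outcome time point, "The 6-month data survey was sent to 43 participants who completed the first and second surveys". The same section concludes: "Given the number of participants who enrolled in the study at least 6 months before May, 2016 (n=101), this gives a completers rate of 32.7" per cent.

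Two other statements matter. Measures and Evaluation Procedures has tumor behavior judged by two investigators from radiological and laboratory reports. The Appendix (Multimedia Appendix 2) shows that participants can upload medical reports in the login area, apart from the questionnaires.

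**The concern.** An ITT comparison needs the outcome to be sought from everyone classified at baseline, whatever they did afterwards. The Results describe a chain in which each survey follows completion of the one before. A participant with a recorded diet who misses the 3-month questionnaire would then receive no 6-month questionnaire. Part of the missing primary-outcome data would come from the study's own follow-up procedure and not from a refusal at 6 months.

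This cannot be left to the analysis plan. A plan can choose a rule for missing outcomes but cannot recover outcomes that nobody requested. If non-responders are dropped, the result is a completers' analysis. If they are counted as not in remission, differences between diets partly follow differences in retention. Comparing remission across diets is the primary aim, and the resulting effect size is meant to support sample size calculations for later studies.

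**Working it through.** **Inputs** (Protocol article, Recruitment and Dropout Rates – Preliminary Experiences, status May 2016)
- Survey 1: 242 invited, 138 completed.
- Survey 2: 109 invited; 72 completed, 4 incomplete, 33 dropped out.
- 6-month survey: 43 sent; 33 completed, 1 incomplete, 9 dropped out.
- Enrolled six months or more earlier: 101. Deaths reported in the whole study: 4. Number of withdrawals: not given.

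**1. The article's own figures.** 33/101 = 32.7% and 33/43 = 76.7% (stated as 77%). Both reproduce. The 2% and 21% printed with a denominator of 33 are in fact 1/43 = 2.3% and 9/43 = 20.9%. In the Discussion, 67.3% is 68/101, not 67/101 (66.3%). These slips do not affect the point.

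**2. Does the flow fit conditional mailing?** Survey 2: 72 + 4 + 33 = 109. The 6-month survey: 33 + 1 + 9 = 43. Each stage closes on the group invited, and each invited group is no larger than the completers before it (109 against 138; 43 against 72). Non-response after reminders is counted as dropout, alongside death and withdrawal. All of this fits a chain conditional on completion, though none of it states a rule.

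**3. Who is affected at survey 2?** 109 − 72 = 37, and 37/109 = 33.9%. This is a ceiling. Some of the 37 had died or withdrawn, and some were not yet due: 72 − 43 = 29 survey-2 completers had not been sent the 6-month survey either. Assume that the due share among the 37 equals that among the 72 (43/72 = 59.7%). Then 37 × 0.597 ≈ 22 were due, still including any deaths and withdrawals.

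**4. Where the whole shortfall sits.** Not sent the 6-month survey: 101 − 43 = 58 (57.4%). Not completed: 101 − 33 = 68 (67.3%). Assume that the overall survey-2 completion rate of 66.1% applies to those due. Then 43/0.661 ≈ 65 were invited to survey 2, which splits the 68 as follows:
- 101 − 65 = 36 lost, or not yet due, before survey 2
- 65 − 43 = 22 lost at survey 2
- 43 − 33 = 10 sent the 6-month survey but not completing it

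On this assumption about 22 of the 68 fall at the step in question, or 22/101 = 21.8%.

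**5. What survey data alone say about the remission rate.** With x remissions among the 33 completers, the rate in 101 lies between x/101 and (x + 68)/101. Values of x are assumed:

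| x | Among completers | Lower bound | Upper bound |
|---|---|---|---|
| 3 | 9.1% | 3.0% | 70.3% |
| 10 | 30.3% | 9.9% | 77.2% |
| 16 | 48.5% | 15.8% | 83.2% |

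The width is always 68/101 = 67.3 points. Had all 43 recipients answered, it would still be 58/101 = 57.4 points. These widths measure total attrition.

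**6. If non-response counts as no remission.** With equal true remission p in two diet groups and retention r1 and r2, the apparent difference is (r1 − r2) × p. Assume retention of 40% and 25%. For p = 10%, 30% and 50% the spurious difference is 1.5, 4.5 and 7.5 points. The article gives no retention by diet, so this illustrates only the mechanism.

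**The case against.** The strongest reply has four parts.

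- **The rule is inferred.** The sentence about the 43 comes from an interim count and does not say that nobody else was or would be invited. The Methods state no condition, and Figure 2, which shows the flow, is not visible here. This stands. The description of both mailings still points to conditional sending, and the two sections need reconciling in any case.
- **The survey is not the only source of the outcome.** Remission is judged from medical reports, which can be uploaded separately. This also stands, so a reader who infers that a 6-month ITT rate cannot be obtained goes too far. However, the upload is started by the participant, and the article describes no request for reports from those who missed a survey.
- **The totals overstate the effect.** A reader might take the 58 of 101 not sent the survey, or the 67-point bounds, as the effect of the mailing practice. The documents do not support that. Those totals also contain early losses, deaths, withdrawals and participants not yet due, and the bounds include 10 who were sent the survey and did not complete it.
- **Attrition is acknowledged and its handling belongs in an analysis plan.** The Bias section names attrition bias and lists reminders and newsletters as countermeasures. The missing-data rule may indeed sit elsewhere and is not criticised here. None of this addresses outcomes that were not requested.

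That those who drop out are sicker is plausible but not shown. The Discussion attributes attrition to anonymity and lack of contact with the study team.

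**Conclusion.** The concern holds in a limited form. The Results indicate that the 6-month survey was sent conditionally on completing both earlier surveys. The Methods state no such condition, and the primary comparison is labelled ITT. Up to 37 of 109 participants invited to the 3-month survey appear not to have been asked for their 6-month outcome. Roughly 22 may have been due by May 2016 if the due share was the same as among completers, before removing deaths and withdrawals. Without their medical reports, the primary result is close to a completers' analysis or rests mainly on assumptions about non-responders. The direction of bias is unknown.

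The conclusion depends on reading the interim account as the working practice, and on few reports arriving unprompted. The 32.7% completers rate shows how serious overall attrition is; it does not measure the effect of the mailing practice.

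**What to change.** Send the 6-month invitation, and those at 12 and 24 months, to every participant with a recorded baseline diet who has not withdrawn or died, whatever earlier surveys they completed. State this in Study Population and Setting so that it agrees with the Results. Before December 2016, re-contact those already skipped with the truncated questionnaire and a request to upload their latest medical report. Keep all of them in the ITT denominator whether or not they reply. If this is not done, label the primary analysis a completers' analysis.

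The restriction to a recorded baseline diet matters, because a registrant with no diet on record cannot be placed in a cohort.

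The cost is a changed mailing list, one extra mailing, and some additional reports for the two existing investigators to read. Response from lapsed participants will probably be low, so the fix reduces the problem without removing it.
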